### Blinding

The study participants and site staff delivering the intervention will remain unblinded due to the nature of the behavioral intervention. The individual blinded to the intervention assignment will carry out the data analysis using the neutrally labeled data set, such as “group A” and “group B.” To ensure consistent and objective measurement of the outcomes, site staff will receive training to rigorously follow the protocol, and regular monitoring and audits will be conducted to ensure compliance. The physician responsible for patient diagnosis and confirming UTI recurrence will remain blinded to the intervention assignment.

### Delivery

The intervention will be delivered as a sticker affixed to antibiotic packaging (boxes or packs) for patients in the intervention group, ensuring easy distribution during medication dispensing, as shown in Fig. 7. The sticker measures 2.5 × 6 cm, allowing for clear visibility and fitting on the box without obscuring important information. The patient will be monitored for medication dispensing at the hospital or nearby pharmacies and drug stores. This format ensures that the patient can take the information home, refer to it later, and be reminded of the importance of adherence after the consultation.

**Fig. 7 Fig7:**
[figure not shown]
Application intervention sticker to antibiotic box **A** vertically and **B** horizontally

### Outcomes

#### Primary outcome

The primary outcome is antibiotic adherence, measured by tracking the pill count at the end of the prescribed antibiotic treatment. This will be expressed as a proportion (number of pills taken/total prescribed) and as a categorical variable (adhered vs. not adhered). Adherence is defined as taking ≥ 90% of the prescribed antibiotic course [32]. This will be assessed during a follow-up visit to the hospital or a home visit.

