## Introduction

### Background

Antibiotic resistance (ABR) presents significant global public health threats, and it is estimated that antibiotic-resistant infections will lead to 10 million deaths each year by 2050 [1]. The overuse and misuse of antibiotics play a significant role in the development of ABR [2–4]. Antibiotic misuse from the demand side includes practices such as obtaining antibiotics without a prescription, self-medication, and failing to adhere to the prescribed treatment, which involves skipping doses or not completing the antibiotic course [5, 6]. To combat the impending threat of ABR, the World Health Organization (WHO) has identified improving rational antibiotic use among individuals as the most essential policy target to mitigate ABR [7].

Non-adherence to antibiotic therapy, a pervasive yet comparatively under-prioritized form of misuse, constitutes a major ABR driver. This behavior stems from multifaceted barriers including forgetfulness, regimen misunderstanding, insufficient awareness about the consequences of incomplete treatment [6, 8], premature discontinuation upon symptom relief, or dose omission due to side effects or financial constraints [6, 9], and comprehension challenges among individuals with limited health literacy, particularly in resource-poor settings [9, 10]. Studies confirm that non-adherence accelerates resistance evolution, as incomplete treatment courses enable bacterial survival and select for resistant strains, progressively eroding antibiotics’ efficacy [11, 12]. Thus, enhancing patient adherence to prescribed antibiotic regimens aligns with WHO’s individual-focused mitigation strategy and is essential to preserve therapeutic effectiveness.

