### Patients’ population and sample size

Participants will include adults (≥ 18 years) with physician-diagnosed uncomplicated UTI who meet all inclusion criteria: (1) confirmed UTI diagnosis, (2) prescribed oral antibiotics (tablet or capsule), (3) having obtained their prescribed medication, (4) willing to participate, and (5) able to provide informed consent.

Patients with polypharmacy (taking five or more medications) [26] are excluded to minimize the risk of confounding factors related to multiple treatment regimens and potential medication interactions that could affect adherence. Patients with complicated UTI (pyelonephritis, sepsis, structural abnormalities) and with multiple comorbidities will be excluded. In addition, patients with cognitive impairment and pregnant or breastfeeding women will also be excluded from the study. Participants may discontinue participation at any time upon request or if they experience clinical deterioration or become ineligible (hospitalization or transfer). All discontinuations and reasons will be documented and summarized in the CONSORT flow diagram.

Eligible uncomplicated UTI patients will be approached during their outpatient visits in the urology department, and written informed consent will be obtained before participation. The patients will be recruited in the current study using the SEAR (Screened, Eligible, Approached, Randomized) framework [27].

The sample size was calculated using R statistical software (version 4.3.0) with “pwr” package (version 1.3.0). Based on our pilot study findings, which demonstrated a 16% improvement in adherence (64.3% in the intervention group vs. 48.3% in the control group), we used this observed effect size (Cohen’s *h* = 0.32) for power calculation. To detect this clinically significant difference in adherence rates with 80% power at a 5% significance level (two-sided test), 152 participants per group (304 total) would be required. Accounting for an estimated 15% attrition rate, informed by our pilot study, we will enroll 179 participants per group (358 total).

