**Fig. 9 Fig9:**
[figure not shown]
SPIRIT schedule of enrollment, interventions, and assessments. Adapted from SPIRIT 2025 guidelines [25]. Notes: X = assessment occurs at this timepoint; — = intervention delivery/exposure period. EOT = end of antibiotic treatment (typically day 3–7 depending on course). Follow-up windows: 1 month (± 7 days), 3 months (± 14 days), 6 months (± 21 days). NA not applicable (no biological specimens collected; harms not systematically assessed due to minimal-risk behavioral intervention)

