### Statistical analysis plan

#### Primary outcome analysis

The primary outcome will be analyzed as a categorical variable (adhered vs. not adhered). The chi-square test or Fisher’s exact test (if expected counts are < 5) will be used for between-group differences. A mixed-effects logistic regression model will estimate the odds ratio (OR) for adherence in the intervention vs. control group, adjusted for baseline characteristics (e.g., age, sex, MPI category, education). Hospital will be included as a random intercept to account for clustering due to stratified block randomization by site.

Based on the multidimensional poverty index [5], which categorizes poverty into four subgroups, namely (1) not deprived, (2) vulnerable to deprivation, (3) deprived, and (4) severely deprived, a subgroup analysis will be carried out to assess the effect of intervention across these subgroups. Results will be reported as adjusted odds ratios (aORs) with 95% confidence intervals (CIs) and *p* values.

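### Prescribed course days and pill number are known at baseline and plausibly predict the ≥ 90% outcome, but are not named as covariates; adding them is a small, free gain in precision

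*Protocol article*

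**What the plan says.** All references are to the protocol article.

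- **Outcome.** Under Primary outcome, "Adherence is defined as taking ≥ 90% of the prescribed antibiotic course". The same paragraph says of adherence: "This will be expressed as a proportion (number of pills taken/total prescribed) and as a categorical variable (adhered vs. not adhered"). Under Primary outcome analysis, only the second form is carried forward: "The primary outcome will be analyzed as a categorical variable (adhered vs. not adhered").
- **Regimens.** Eligibility requires "prescribed oral antibiotics (tablet or capsule"), with no restriction on drug, pill number or duration. The notes to Fig. 9 give "EOT = end of antibiotic treatment (typically day 3–7 depending on course").
- **Timing.** Patients must already have obtained their medicine to be eligible, and Baseline data screens on prescription filling. The prescription therefore precedes allocation.
- **Model.** The primary mixed-effects logistic regression is "adjusted for baseline characteristics (e.g., age, sex, MPI category, education"), with hospital as a random intercept.
- **Imputation.** The ITT section lists age, sex, MPI category and baseline knowledge and attitude scores, without an 'e.g.'.
- **Randomisation.** It is blocked within hospital and not stratified by course.

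**The concern.** Whether a patient counts as adherent depends on behaviour and also on what was prescribed, through two routes.

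1. **Early stopping.** The Background lists "premature discontinuation upon symptom relief" among the reasons for non-adherence, and the sticker is aimed at that behaviour. Someone who stops after day 3 has completed a 3-day course but only 3/7 = 43% of a 7-day course.
2. **The cut itself.** On a short pack, 90% means every pill; on a larger pack, one or two pills may be left.

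A baseline variable that predicts the outcome is worth having in the model because it removes explainable variation from the treatment comparison. It is also worth having in the imputation model, which is meant to hold predictors of outcome and missingness. The stake is some power and a better-informed imputation. The validity of the primary analysis is not in question.

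**Working it through.** **1. The plan's own figure.** Inputs from the sample-size section: 64.3% versus 48.3%, two-sided 5%, 80% power. Cohen's h = 2·asin√0.643 − 2·asin√0.483 = 0.324. Then n = 2·((1.960 + 0.842)/h)² = 149.5, so 150 per group; with h rounded to 0.32 it is 153.3, so 154. The stated 152 lies between the two. Attrition: 152/0.85 = 178.8, so 179. The sample size reproduces, and nothing below alters it.

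**2. What the cut allows.** The largest k with (n − k)/n ≥ 0.90 is floor(n/10).

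| Pills prescribed | Misses allowed |
|---|---|
| 1–9 | 0 |
| 10–19 | 1 |
| 20–29 | 2 |

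Three to seven days at an assumed 1 to 4 pills a day gives 3 to 28 pills, so all three rows can occur.

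**3. Effect of the cut alone.** Assume every patient takes each pill independently with probability 0.95. Then P(adherent) = P(Binomial(n, 0.95) ≥ n − floor(n/10)).

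| Pills | 3 | 6 | 9 | 10 | 14 | 20 | 21 |
|---|---|---|---|---|---|---|---|
| P(adherent) | 0.857 | 0.735 | 0.630 | 0.914 | 0.847 | 0.925 | 0.915 |

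The pattern is a sawtooth, with a 28-point jump from 9 to 10 pills. Calibrated to 48.3% control adherence over an equal mix of 6, 9, 10, 14, 20 and 21 pills, control rates run from 0.30 to 0.64 if misses are independent. With a within-patient correlation of 0.5 they run only from 0.42 to 0.53.

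**4. Effect of early stopping alone.** On courses of 3 to 7 days, losing the last full day already fails the cut (at best 6/7 = 86%). With an assumed constant daily probability s of continuing, adherence on a d-day course is s^(d−1). For an equal mix of 3 and 7 days, a mean of 48.3% gives s = 0.817: 0.817² = 67% on 3 days and 0.817⁶ = 30% on 7 days. Here longer courses do worse, whereas the pill allowance is most lenient on larger packs.

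**5. Power at 152 per arm.** Simulated trials were calibrated to 48.3% versus 64.3%. An unadjusted test was compared with one stratified by course, as a stand-in for the adjusted model; hospital effects were ignored.

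| Assumed equal mix | Mechanism | Unadjusted | Adjusted |
|---|---|---|---|
| 3, 7 days | stopping | 81% | 85% |
| 3, 5, 7 days | stopping | 81% | 83% |
| 3 to 7 days | stopping | 81% | 82% |
| 5, 7 days | stopping | 81% | 82% |
| 6, 10, 14 pills | cut | 81% | 81% |
| 3, 6, 9, 10, 14 pills | cut | 81% | 83% |
| 6, 9, 10, 14, 20, 21 pills | cut | 81% | 82% |

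A model with both mechanisms gives 81% to 82–84%. Each figure carries simulation error of a fraction of a point, so the smallest gains are close to nil.

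**6. Bias and type I error.** Under no treatment effect, rejection rates in the pill mixes were 0.044–0.049 unadjusted and 0.050–0.053 stratified. Both are about 5%.

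**The case against.** - **The covariate list is open.** It begins with 'e.g.', so course length is unnamed rather than excluded, and a fuller analysis plan that is not shown may add it. This stands, and is why the point is offered as an improvement. The imputation list has no such qualifier, but it too could be completed elsewhere.
- **A reader might infer that course length drives the outcome.** The documents do not support that. They give no distribution of pills or days and no adherence by course. The two mechanisms can pull in opposite directions, the effect of the cut is not monotone, and it shrinks when misses cluster within patients.
- **A reader might treat chance imbalance in course length as an extra error in the estimate.** It is not. The prescription precedes randomisation, so the arms are balanced in expectation. For the 3- and 7-day mix, chance imbalance moves the risk difference by 1.96 × √(2 × 0.25/152) × 0.37 = ±4.2 points (95% range). That already lies inside the ordinary interval of 1.96 × √[(0.483 × 0.517 + 0.643 × 0.357)/152] = ±11.0 points, and is (4.2/11.0)², or about 14%, of its variance. Adjustment recovers that part as precision; it does not correct a bias.
- **Days or pills?** The allowance depends on pill number and early stopping on days, so one linear term for either would miss the other. This is right, and the fix uses both.

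**Conclusion.** The point holds as a free improvement with a small gain. Prescribed days and pill number vary, are settled before allocation, plausibly predict the binary outcome, and are not named in either covariate list. Adjusting for them adds about 1 to 4 points to a power of about 81%. The upper end needs an even split between 3- and 7-day courses with early stopping as the only mechanism; narrower mixes gain a point or less. These figures rest on assumed course mixes, assumed patterns of missed doses and calibration to the pilot rates. There is no bias to remove, the type I error is sound, and the ≥ 90% definition needs no change.

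**What to change.** Keep the ≥ 90% definition. Prespecify two baseline covariates in the primary mixed-effects logistic model and in the imputation model:

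1. prescribed course duration in days;
2. allowed-miss category by prescribed pill number: under 10, 10–19, 20 or more.

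Take both from the prescription record rather than from anything observed after allocation. Because the odds ratio is conditional on the covariates, fix the list before unblinding.

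Optionally, add a supportive analysis of the proportion of pills taken, which the protocol already defines and which does not depend on the cut.

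The cost is two covariates. Pill number is already the outcome's denominator, and duration should stand on the same prescription record. There are no new visits, no extra patients and no change to treatment or eligibility.

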#### Secondary outcomes

##### UTI recurrence

This will be measured using a dichotomous question (yes, no). The physician will confirm the recurrence of UTI.

##### Knowledge and attitude

Knowledge and attitude are critical behavioral determinants of antibiotic adherence and clinical outcomes [33, 34]. Theoretical models such as the Knowledge, Attitudes, and Practice (KAP) model and the Theory of Planned Behavior (TPB) suggest that improved knowledge and positive attitudes toward antibiotic use influence adherence behaviors, which in turn reduce clinical risks such as UTI recurrence [33, 35].

Patient knowledge of antibiotic use, antibiotic resistance, and the importance of completing the treatment will be assessed using a 10-item questionnaire. The item was developed based on the previously reported studies [36–38]. The response will be collected as “true” and “false.” The true response will be scored 1 point and the incorrect response as 0. Attitude toward antibiotic use and adherence will be measured using a 5-item Likert scale, developed based on the previous studies [38–40], with responses ranging from 1 (strongly disagree) to 5 (strongly agree).

The content validity of the tools was established through expert review by two academicians having similar academic backgrounds, one pharmacist and one infectious disease specialist. Discrepancies in item wording were resolved by consensus. A pilot study was conducted with 60 patients. Preliminary reliability demonstrated acceptable internal consistency: Cronbach’s alpha for knowledge = 0.71, and for attitude = 0.73, showing valid internal consistency. Content Validity Index (CVI) analysis showed a scale-level CVI of 0.75 for knowledge and 0.83 for attitude, indicating acceptable validity.

### Data collection

#### Data collection procedure

Data will be collected utilizing EpiCollect5, a secure, cloud-based platform for mobile data collection that facilitates real-time monitoring and centralized management [41]. The principal investigator will oversee the entire data collection process. Three designated data collection supervisors will be appointed as “project managers” within the EpiCollect5 system. Each supervisor will be responsible for managing a team of trained data collectors operating at various field sites. The supervisors will monitor data quality, provide on-site guidance, and ensure compliance with standardized data collection protocols. The principal investigator will perform regular remote inspections via the EpiCollect5 dashboard to verify data completeness, consistency, and accuracy. This tiered supervision model enables prompt identification and resolution of field-level challenges, fosters data integrity, and guarantees the uniform application of procedures across sites. Each participant will be assigned a unique study code. Access to the project database is restricted to authorized study investigators using role-based permissions. All data collectors will undergo standardized training prior to field deployment to uphold inter-rater reliability and ethical standards.

#### Baseline data

At the start of the study, baseline demographic and patient data will be collected. Additionally, questionnaires regarding knowledge and attitudes will also be collected from all participants. During this stage, patients will be screened based on their prescription filling. Those who filled the prescription will be included for follow-up, while those who did not fill the prescription will be excluded, and the reasons for not filling the prescription will be identified. Data collectors will be trained for intervention implementation and data collection.

#### Follow-up data

At the follow-up stage, pill counts will measure adherence, and structured questionnaires will be administered to assess changes in knowledge and attitudes regarding antibiotic use. Then, the next follow-up will be done after 1 month, 3 months, and 6 months. At each follow-up, either at the hospital or home visit, the pill count will be performed by the trained data collectors. Returned blister packs will be checked against prescription records. Any discrepancies between the baseline dispensed quantity and the physical count will be documented in site monitoring logs and reviewed by the site supervisor. If packaging is not returned, adherence via pill count will be coded “not verifiable” and treated as missing for the primary pill-count outcome. The details are given in Fig. 8. The overall schedule of enrollment, interventions, and assessments is illustrated in Fig. 9.

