#### Intention-to-treat (ITT) and per-protocol (PP) analysis

##### ITT analysis

The primary analysis will follow the intention-to-treat (ITT) principle and include all randomized participants. We will handle participants with lost to follow-up, missing outcomes, and covariate data using multiple imputations by chained equations (MICE) under a missing-at-random (MAR) assumption [42, 43]. The imputation model will include the primary outcome, baseline covariates predictive of outcome and missingness (age, sex, MPI category, baseline knowledge, and attitude scores). We will generate at least m = max (20, % missing × 1) imputations, fit the planned analysis model within each imputed dataset, and combine estimates using Rubin’s rules [44]. The participants who formally withdraw consent will be excluded from the analysis.

To assess robustness to departures from MAR, we will conduct sensitivity analyses: (1) a complete-case analysis; (2) pattern-mixture/delta-adjustment sensitivity analyses that impose plausible shifts (delta) to imputed outcomes under missing-not-at-random (MNAR) scenarios; and (3) a conservative worst-case/best-case bounds analysis for the primary binary outcome. Results from sensitivity analyses will be reported alongside the primary multiple imputation results and used to assess the robustness of conclusions regarding treatment effect.

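### Treating adherence as missing when the pack is not returned, then imputing under MAR from baseline variables, lets a behaviour after randomisation decide who is observed; the odds ratio is biased only if completers' return relative to non-completers' differs by arm

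*Protocol article*

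**What the plan says.** The primary outcome is a pill count at the end of treatment, split at a threshold: "Adherence is defined as taking ≥ 90% of the prescribed antibiotic course". On where it is done, the Primary outcome section says: "This will be assessed during a follow-up visit to the hospital or a home visit". Under Follow-up data the count rests on the packaging: "Returned blister packs will be checked against prescription records". The rule for absent packaging is: "If packaging is not returned, adherence via pill count will be coded “not verifiable” and treated as missing for the primary pill-count outcome".

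The Delivery section states: "The intervention will be delivered as a sticker affixed to antibiotic packaging (boxes or packs) for patients in the intervention group". It adds: "This format ensures that the patient can take the information home, refer to it later, and be reminded of the importance of adherence".

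The ITT analysis section handles missing outcomes "using multiple imputations by chained equations (MICE) under a missing-at-random (MAR) assumption". The variables listed for the imputation model are the primary outcome, age, sex, MPI category and baseline knowledge and attitude scores. The same section plans a complete-case analysis, delta-adjusted analyses under MNAR, and worst-case/best-case bounds.

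**The concern.** A participant who finished the course, threw away the empty blisters and attends the visit has a missing outcome. One who stopped early still has pills and a pack to show, though perhaps less wish to show them. So whether the outcome is observed may depend on the outcome itself. It may also depend on arm, since only one arm's packaging carries material meant to be kept and looked at again, and its message about stopping early may affect who is willing to show the pack.

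No listed imputation variable says why a pack is absent. Imputation under MAR therefore gives non-returners roughly the adherence of returners with similar baseline data. If that is wrong to a different degree in the two arms, the primary odds ratio is wrong, and the reason for non-return cannot be recovered once the visit has passed.

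Discretion also enters. The visit may be at the hospital or at home, and the rule as stated does not make a home attempt a condition for declaring the outcome missing. On blinding: "The study participants and site staff delivering the intervention will remain unblinded due to the nature of the behavioral intervention". Under Baseline data, the data collectors are trained for both intervention implementation and data collection.

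**Working it through.** **Inputs from the protocol** (Patients' population and sample size): adherence 64.3% vs 48.3%, 80% power, two-sided 5%, 152 per group, 15% attrition, 179 per group. **Assumed, because the documents give none:** all pack-return rates.

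**The plan's own figures.** h = 2·asin(√0.643) − 2·asin(√0.483) = 0.324. n = 2(1.960 + 0.842)²/h² gives 149.5 with h = 0.324 and 153.3 with h = 0.32, and the stated 152 lies between. 152/0.85 = 178.8, so 179. The sample size is not in dispute. The true odds ratio at the planned rates is (0.643/0.357)/(0.483/0.517) = 1.93.

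**What the rule does.** Let p be true adherence in an arm, and a and n the return rates of completers (adherent) and non-completers. Verifiable adherence = p·a/[p·a + (1−p)·n]. The observed odds in an arm are therefore the true odds times a/n, and

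observed OR = true OR × (a/n in intervention) ÷ (a/n in control).

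I take the baseline covariates to be uninformative about return and imputation to be done within arm, so the MAR estimate is close to the estimate in returners.

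**Two patterns that leave the OR intact**
- Completion only, a = 75% and n = 95% in both arms: 58.7% vs 42.4% is observed instead of 64.3% vs 48.3%. Both rates are too low, but the OR stays 1.93 and null rejection stays 5%.
- Arm only, 95% return in intervention and 75% in control whatever the adherence: a/n = 1 in each arm, so there is no bias.

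**Patterns that bias the OR** (true adherence 48.3% in both arms)

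| Control a / n | Intervention a / n | Observed control | Observed intervention | Difference | OR |
|---|---|---|---|---|---|
| 80% / 95% | 95% / 95% | 0.3864/0.8776 = 44.0% | 48.3% | +4.3 | 1.19 |
| 80% / 90% | 90% / 80% | 0.3864/0.8517 = 45.4% | 0.4347/0.8483 = 51.2% | +5.9 | 1.27 |
| 90% / 75% | 90% / 90% | 0.4347/0.8225 = 52.9% | 48.3% | −4.6 | 0.83 |

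The third row uses the same kind of premise (early stoppers in control reluctant to show the pack, the sticker evening out return in the other arm) and reverses the sign. These rows are illustrations, not limits. The opposite corner of the assumed range (control 75%/95%, intervention 95%/75%) gives 0.3623/0.8534 = 42.4% vs 0.4589/0.8466 = 54.2%, or +11.8 points, and swapping the arms gives −11.8.

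For scale on type I error: control completers 75%, intervention completers 90% and all non-completers 95% give a null OR of (0.90/0.95)/(0.75/0.95) = 1.20. Two-sided rejection is 12.7% in a two-proportion z-test with 179 × the return rate per arm.

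**Bounds.** At 15% missing per arm around the planned 16 points: 0.85·0.643 − (0.85·0.483 + 0.15) = −1.4 points, and 0.85·0.643 + 0.15 − 0.85·0.483 = +28.6 points. The 15% is the protocol's overall attrition, not a pack non-return rate, so this is only an illustration.

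**Arm in the imputation model.** The listed variables do not name arm. If it were really left out and 15% of outcomes were filled from the pooled rate of 56.3%, the rates would be 0.85·0.643 + 0.15·0.563 = 63.1% and 0.85·0.483 + 0.15·0.563 = 49.5%. That is 13.6 points instead of 16.0, and an OR of 1.74.

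**The case against.** A reader might infer that the rule biases the trial in favour of VISTA, or that any difference in return between arms biases the odds ratio. The documents support neither. The second is false by the identity above. The first needs return rates that the documents do not give, and plausible premises point both ways.

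The other side also has these points:
- **The planned sensitivity analyses are real.** Wide bounds do not discredit the delta analysis. In the +5.9 scenario, true adherence among non-returners is 0.0966/0.1483 = 65.1% in control and 0.0483/0.1517 = 31.8% in intervention. Deltas of about +20 and −19 points would recover the null. This stands, but it needs deltas that differ by arm and some basis for choosing them, and the primary estimate stays as it was.
- **The sticker may be on the outer box while the count uses the blisters.** The text is mixed: Delivery speaks of boxes or packs. A reason to keep the box is not surely a reason to keep the blisters. This weakens the arm mechanism without removing it.
- **Operational detail may be in the full protocol.** Home visits are already a mode of assessment, consent tells both arms about pill counts, and treatment typically ends by day 3 to 7, which leaves little time to discard packs. Silence on a keep-the-pack instruction is not itself a finding. The point rests on what is stated: the missing-outcome rule combined with MAR imputation from baseline variables.
- **Self-reported pills left would weaken an objective outcome.** This stands. Participants are unblinded, and the Discussion already notes social desirability bias in self-report.

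**Conclusion.** The point holds as a doubt about the MAR assumption for unreturned packs, not as a demonstrated bias. The missing-outcome rule makes observation of the primary outcome depend on a behaviour after randomisation that completion and arm may both affect. The odds ratio is affected only if the completer to non-completer return ratio differs between arms; otherwise at most the two adherence rates are distorted. In the three tabulated scenarios, with assumed return of 75% to 95% and no true effect, the spurious difference runs from −4.6 to +5.9 points, against a planned effect of 16. Neither size nor sign can be taken from the documents. The delta and bounds analyses lessen the problem without changing the primary estimate. It is worth correcting because the correction is cheap and the information can be collected only at the visit.

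**What to change.** 1. At dispensing, give both arms the same instruction to keep the box and all blisters, empty or not, until the end-of-treatment visit.
2. Code the count as not verifiable only after the home visit already provided for has been attempted, by the same rule in both arms.
3. When the pack is still absent, record the reason (discarded empty, discarded with pills, lost). Use it as an auxiliary variable in the imputation model, and name arm in that model. Use the participant's stated number of pills left in a sensitivity analysis only.
4. Report pack return by arm, and let the delta values differ by arm.

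The cost is a sentence at dispensing, short additions to the visit form and some additional home visits. The instruction slightly raises awareness of the count, equally in both arms. The Trial status section expected recruitment to end on 30 September 2025, so steps 1 to 3 help only participants whose end-of-treatment visit is still to come. Step 4 and naming arm in the imputation model remain possible until the analysis is fixed.
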